## Abstract

**Introduction:**

Improving outcomes from sepsis in children is a WHO Global Health Priority, yet mortality from sepsis remains high, particularly in low- and middle-income countries (LMICs). This database from children with community-acquired childhood sepsis in LMICs and some high-income countries will allow analysis of the burden of disease, including incidence, severity and outcomes. Understanding these aspects of sepsis care is fundamental for the design and conduct of future international interventional trials to improve childhood sepsis outcomes.

**Methods and analysis:**

This multicountry retrospective observational study will include children up to 18 years of age presenting to emergency departments with suspected sepsis, defined as admission to hospital for treatment with intravenous antibiotics plus (1) a provisional diagnosis of sepsis and/or (2) treatment for suspected sepsis (operationalised as the administration of one or more fluid bolus to treat impaired perfusion or vasoactive infusion). Presenting characteristics, management and outcomes will be collected. These will include vital signs, serum biomarkers, intravenous fluid administration for the first 24 hours of hospitalisation, organ support therapies delivered, antimicrobial use, microbiological diagnoses, hospital and intensive care unit length of stay, and mortality censored at hospital discharge or 30 days from enrolment (whichever occurs first).

**Ethics and dissemination:**

Central ethics approval was received from the Royal Children’s Hospital of Melbourne, Australia Human Research Ethics Committee (HREC/100648/RCHM-2023). Each international site will be required to obtain local Institutional Research Ethics Board approval. The findings will be disseminated in peer-reviewed journals, at academic conferences and through lay media. A cleaned study database and individual site-level data will be made available to site investigators upon completion of the study.

**Trial registration number:**

This study was registered with the Australian and New Zealand Clinical Trials Registry on 23 January 2024 prior to commencement of recruitment (ACTRN12624000052538).

STRENGTHS AND LIMITATIONS OF THIS STUDYThis study is being conducted across multiple emergency departments (EDs) primarily in low- and middle-income countries using standardised inclusion criteria, allowing comparison between populations.This study will demonstrate the feasibility of manual data extraction and transfer from multiple countries with different healthcare systems and research infrastructure.This study uses similar inclusion criteria to those that may be used in future interventional trials, paving the way for ongoing international collaborative research.The potential for variability in case identification and data collection has been mitigated using data dictionaries and standard operating procedures, site training and piloting of clinical report forms, delegation logs and ongoing data quality monitoring in keeping with good clinical practice.While multiple EDs are included, most are tertiary referral centres and may not reflect the population seen in community, rural and regional centres.

## Introduction

 Sepsis is an important global health issue. Over 25.2 million children per year worldwide develop sepsis, resulting in 3.4 million deaths, most of them in children younger than 5 years of age.^1^ The hospitalisation cost per child with sepsis in the USA alone is estimated at US$26 592, resulting in an annual expenditure of US$7.31 billion representing 18.1% of nationwide paediatric hospitalisation costs in the USA in 2019.^2^ Reducing childhood deaths from sepsis is a WHO Global Health Priority and is essential if the United Nations Sustainable Development Goals are to be achieved.^3^

Despite advances in public health, prevention and treatment of many infectious diseases, invasive infections and sepsis remain leading causes of preventable childhood death worldwide.^4^ Mortality from sepsis remains substantial, even in high-income countries (HICs).^5^ Children with sepsis are disproportionately affected in terms of disability-adjusted life years compared with adults with sepsis, due to premature death (years of life lost) and long-term disabilities in sepsis survivors (years lived with disability).^6^ Despite decades of research into the treatment of sepsis, sepsis-specific mortality remains unchanged. Any reduction in sepsis mortality mirrors that of children hospitalised for non-infectious causes.^7^ This may in be part due to an increasing number of patients surviving with high-risk conditions, such as extreme prematurity, acquired or innate immunodeficiency, or the presence of indwelling vascular catheters.^8^

Many challenges contribute to the lack of accurate reporting of sepsis epidemiology, severity and therapies in children, with the major contributor being inconsistency in the methods used for case ascertainment. International Classification of Disease codes have been used to retrospectively identify children with sepsis or infection-related organ dysfunction, with a sevenfold difference in incidence found between these two case ascertainment methods.^9^ Case ascertainment using International Sepsis Consensus Conference criteria has been found to be discordant with clinician ascertainment of sepsis, with an inter-rater agreement (kappa) of 0.57.^10^ Recently, the Society of Critical Care Medicine has derived and validated the international consensus-based Phoenix criteria to diagnose and report sepsis in children, based on measures of dysfunction of four organs after the initial 24 hours of hospitalisation.^11^ There remain questions, however, regarding the applicability of these criteria in the emergency department (ED) and early in hospitalisation, the impact of missing organ dysfunction data (particularly in low- and middle-income countries (LMICs)) and the test characteristics of the Phoenix sepsis criteria for predicting mortality.^12 13^ Ideally, data used as diagnostic criteria from across countries are collected in a way that allows comparison between populations.

In an international collaboration between emergency physicians, paediatricians and intensivists, this study will develop the first database for children with community-acquired childhood sepsis in LMIC and select HIC. We will describe sepsis prevalence, severity and outcomes. We will report current management practice and antimicrobial use. We will apply diagnostic criteria and risk stratification criteria to allow standardised comparisons across diverse populations. This study will provide the critical understanding of the epidemiology of children with suspected sepsis as a basis for future interventional trials.

## Methods

### Design

This is a multicountry retrospective observational study. Studies conducted using this database will follow the Strengthening the Reporting of Observational Studies in Epidemiology guidelines for the reporting of observational studies and the Standards for the Reporting of Diagnostic Accuracy studies (STARD) guidelines for the validation of sepsis organ dysfunction criteria using methodology applied to similar bi-national (Australia and New Zealand) sepsis database.^12 14 15^

### Patient and public involvement

The research team includes a parent consumer lead with lived experience caring for a child with infection-related conditions including sepsis. This parent consumer and a hospital family advisory committee reviewed the study for acceptability of data collection. Their feedback will be included in publications and presentations of study results. Study data and outcomes collected include those deemed of high importance to parents and clinicians.^16 17^

### Setting and participants

The study will take place at multiple EDs who individually see at least 20 000 children per year. Out of a total of 34 sites, 25 are in LMICs and 9 in HICs (see online supplemental Material). Study sites were identified through known contacts. No approached sites declined participation. The central coordinating site for the study is the Murdoch Children’s Research Institute, which is affiliated with The Royal Children’s Hospital Melbourne.

#### Inclusion and exclusion criteria

Patients up to 18 years of age who present to a participating ED for treatment of suspected sepsis will be included. Suspected sepsis will be defined as children with the intention to admit to hospital for parenteral antibiotics and (1) a provisional (admission) diagnosis of sepsis, septicaemia or septic shock AND/OR (2) treatment for sepsis, operationalised as treatment with one or more fluid boluses to treat impaired perfusion, not dehydration (defined as a fixed volume of fluid administered over <30 min) or vasoactive infusion. We chose these inclusion criteria because prior studies had indicated that an admission diagnosis of sepsis alone did not identify a substantial proportion of febrile children started on a vasoactive infusion and treated in the intensive care unit (ICU).^18^ We included ‘treatment for suspected sepsis’ as an inclusion criterion as prior studies had identified that a substantial proportion of patients with infection requiring ICU-level care did not have an admission diagnosis of sepsis.^18^ This was operationalised using the administration of a fluid bolus to treat poor perfusion as this was the initial treatment for sepsis recommended in all guidelines and pathways at participating sites in addition to the use of intravenous antibiotics.^19^ The requirement for the fluid bolus to treat impaired perfusion was included as prior studies identified dehydration as the most common indication for fluid bolus administration.^20^ These criteria were used in a bi-national sepsis epidemiological study (SENTINEL; Australia and New Zealand) and differ from the inclusion criteria used in the derivation and validation of the Phoenix sepsis criteria (suspected infection operationalised as receipt of parenteral antimicrobials and microbiological testing within the first 24 hours of encounter).

Patients who are not admitted through the ED (such as direct inter-hospital ICU transfers) and patients who are admitted to another hospital ward >24 hours prior to ED transfer will be excluded due to difficulty obtaining initial vital signs and biomarkers. Patients presenting with trauma will be excluded.

### Aims

Primary and secondary aims are listed in Box 1.

Box 1Primary and secondary aimsPrimary aimTo create an international sepsis database and collect data over a 1-year periodSecondary aimsTo aggregate and analyse sepsis data and describe:Sepsis prevalence, severity and outcomes in children hospitalised with suspected community-acquired sepsis.The microbiology, antibiotic use patterns and antimicrobial stewardship practices in hospitalised children with suspected sepsis.The management of hospitalised children with suspected sepsis.To apply standardised diagnostic criteria to this international cohort of children with suspected sepsis (SIRS, Phoenix sepsis criteria)To apply standardised risk stratification tools to this international cohort of children with suspected sepsis (SIRS, pSOFA, qSOFA, qPELOD-2, Phoenix sepsis score)To develop feasible inclusion criteria and outcomes, and establish feasibility of data collection and transfer, to be used in the design and conduct of future interventional trials in children with suspected sepsispSOFA, paediatric Sequential Organ Failure Assessment; qPELOD-2, quick Paediatric Logistic Organ Dysfunction-2; qSOFA, quick Sequential Organ Failure Assessment; SIRS, systemic inflammatory response syndrome.

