**Figure 1 F1:**
[figure not shown]
Participant enrolment flow chart. ED, emergency department.

Enrolled participants will have their medical records reviewed, and relevant de-identified data will be extracted and entered directly into a password-protected Research Electronic Data Capture (REDCap) electronic database. Data to be extracted are outlined in box 2. Age was measured in months for children <2 years of age and in years for children ≥2 years of age. Indigenous status was defined using local ethnicity criteria, where applicable (eg, Aboriginal or Torres Strait Islander in Australia; Māori or Pasifika in New Zealand). Comorbidities were defined using the Pediatric Complex Chronic Condition system.^21^ We included primary site of infection and primary pathogen causing sepsis in the data collected. We did not collect inflammatory markers such as C-reactive protein or procalcitonin.

Box 2Data to be collected by all participating EDs by time pointInitial ED attendanceDetailed patient demographic information (age, sex, Indigenous status, comorbidities)Vital signs (^β^HR, MBP, SBP, RR, SpO2, GCS score, CRT)Pathology tests (^χ^VBG, FBC, UEC, LFT, coagulation profile, troponin)Therapies administered (antibiotics, oxygen, fluids—bolus/maintenance/drug administration line, steroids, organ support)Admission diagnosisDuring hospital stayDisposition (hospital ward, ICU)Vital signs (6, 12, 18 and 24 hours from ED arrival)Pathology tests (6, 12, 18 and 24 hours from ED arrival)Therapies administered (duration of hospitalisation censored at 30 days)ICU and hospital length of stay (censored at 30 days)Discharge diagnosisResults of all microbiological testsIn-hospital mortality (censored at 30 days)CRT, capillary refill time; ED, emergency department; FBC, full blood count; ICU, intensive care unit; LFT, liver function test; MBP, mean blood pressure; RR, respiratory rate; SBP, systolic blood pressure; UEC, urea electrolytes creatinine; ^α^GCS, Glasgow Coma Scale; ^β^HR, heart rate; ^χ^VBG, venous blood gas.

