## Discussion

This is the first international database that will allow a comprehensive description of sepsis epidemiology. This will improve the understanding of global sepsis incidence, severity and outcomes, and allow for comparison between diverse populations. Prior global epidemiological studies have focused on the point prevalence of sepsis in critical care populations or global estimates of disease burden.^5 27^ Building on these prior efforts, we will explore differences in aetiology of sepsis and allow comparisons of management of sepsis including patterns of antimicrobial use between populations. Standardised criteria for sepsis diagnosis and risk stratification will be applied to the study cohort, providing a benchmark for between-population comparison. Finally, this study will provide baseline data and feasibility data for the conduct of future interventional trials.

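### The Abstract and Discussion promise sepsis incidence, even globally, but contact-selected, mostly tertiary EDs with no listed denominator cannot deliver it; prevalence within the enrolled cohort can be estimated.

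*Protocol article*

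**What the plan says.** **Claims about frequency.** The introductory part of the Abstract states that the database "will allow analysis of the burden of disease, including incidence, severity and outcomes". The Discussion says of the database: "This will improve the understanding of global sepsis incidence, severity and outcomes, and allow for comparison between diverse populations". The aims (Box 1) use a different term and name a population: "Sepsis prevalence, severity and outcomes in children hospitalised with suspected community-acquired sepsis". Separate aims in the same box apply SIRS and the Phoenix sepsis criteria to the cohort of children with suspected sepsis.

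**Design.** Under Setting and participants: "Study sites were identified through known contacts". The sites are "multiple EDs who individually see at least 20 000 children per year", and "Out of a total of 34 sites, 25 are in LMICs and 9 in HICs". The Inclusion and exclusion criteria leave out children not admitted through the ED, with direct inter-hospital ICU transfers as the example. The Discussion adds that most sites are tertiary referral centres.

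**Data.** On extraction, the article says: "Enrolled participants will have their medical records reviewed, and relevant de-identified data will be extracted". Box 2 then lists demographics, vital signs, laboratory tests, therapies, diagnoses, microbiology, length of stay and mortality. All are items on an individual child. No count of ED attendances, of admissions, or of a catchment population is listed. Research staff do screen each ED's attendance records at least once every 14 days.

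**Sample size.** The target is more than 5000 children in 12 months. No formal calculation was made, and the reason given is a lack of earlier data on sepsis incidence.

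**The concern.** Incidence needs new cases over a defined population at risk and a defined time. The design supplies cases and time but no population. If the claim stays as worded, the raw number of cases per site or per country is the only material from which a reader could judge burden. Those numbers mix disease frequency with ED size, referral role and the differences in clinicians' thresholds that the Discussion itself concedes. A comparison of LMIC with HIC sites on that basis would not be a comparison of incidence. It matters because the study is meant to inform the design of later interventional trials, where expected cases per site is a planning figure.

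A lesser problem lies in Box 1. It names prevalence without saying which criterion defines sepsis. SIRS and Phoenix can classify the same children differently, so one cohort can yield more than one prevalence.

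**Working it through.** The article gives no incidence figure and no sample size formula, so there is no stated result to reproduce. The check asks what numerator and denominator each quantity needs, and whether the listed data hold them.

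**1. Prevalence of criteria-defined sepsis among suspected cases.**
- Numerator: enrolled children meeting SIRS or Phoenix. Denominator: all enrolled children. Both are in the database, so this is estimable.
- Precision with n = 5000 over 34 sites (mean 5000/34 = 147.1 per site), taking a proportion p and an intraclass correlation ICC, both assumed:
  - DEFF = 1 + (147.1 − 1) × ICC
  - 95% half-width = 1.96 × √(DEFF × p(1 − p)/5000)

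| Assumed p | No clustering | ICC 0.01 (DEFF 2.46) | ICC 0.05 (DEFF 8.30) | ICC 0.10 (DEFF 15.61) |
|---|---|---|---|---|
| 10% | 0.8 points | 1.3 | 2.4 | 3.3 |
| 25% | 1.2 points | 1.9 | 3.5 | 4.7 |
| 50% | 1.4 points | 2.2 | 4.0 | 5.5 |

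The formula treats sites as equal in size. Even so, the table shows that this quantity is within reach.

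**2. Suspected sepsis per ED attendance or per ED admission.**
- Numerator: enrolled children. Denominator: not listed in Box 2. The only related figure is the site minimum of 20 000 children a year.
- Floor on attendances: 34 × 20 000 = 680 000 a year (LMIC 25 × 20 000 = 500 000; HIC 9 × 20 000 = 180 000).
- Ratio at the floor for exactly 5000 enrolled: 1000 × 5000/680 000 = 7.35 per 1000.
- With true attendances at an assumed multiple of the floor:

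| Multiple of floor | Attendances | 5000 enrolled, per 1000 |
|---|---|---|
| 1 | 680 000 | 7.4 |
| 1.5 | 1 020 000 | 4.9 |
| 2 | 1 360 000 | 3.7 |
| 3 | 2 040 000 | 2.5 |

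The same case count fits a threefold range of rates, so an eligibility minimum cannot stand in for a measured denominator. The article gives no figure for admissions.

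**3. Population or global incidence.**
- Denominator: children living in the areas served. None is given.
- Sites are not a probability sample, and most are tertiary, so their cases cannot be weighted up to a wider population.
- The numerator is incomplete too, because cases reaching hospital by routes other than the ED are excluded.
- Attendance counts would repair item 2 but not this one. Nor would a larger enrolment.

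**The case against.** The strongest case for the plan has four parts.

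- **The aim names its own denominator.** Box 1 speaks of children hospitalised with suspected sepsis, and the diagnostic criteria are applied to that cohort. A reader might infer that neither prevalence nor incidence can be estimated and that this aim is unanswerable. The documents do not support that. The within-cohort prevalence is computable, and Box 2 covers severity and outcomes. This part of the objection stands in full.
- **A condensed article cannot show that attendance counts go unrecorded.** Box 2 describes what is taken from enrolled children's records. The enrolment flow chart, the site supplement and the manual of operations are not shown, and attendance records are already being screened. This stands as far as it goes: it would be wrong to assert that no counts exist. Screened counts would still supply neither a catchment population nor a representative set of sites.
- **The Discussion promises only better understanding of global incidence, and the statistical section plans no incidence estimate.** That is true of the Discussion's wording. The Abstract is more direct: it lists incidence among the things the database will allow to be analysed.
- **Limits on representativeness are disclosed.** The tertiary setting, varying thresholds and a reach confined to major urban centres are all acknowledged. The listed limitations nevertheless do not say that incidence is out of reach, although they name several other measures that were not collected.

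Two further inferences should be resisted. The 7.4 per 1000 figure is not a ceiling for this study, because the target is more than 5000. Nor does any section equate the Abstract's incidence with Box 1's prevalence, so it is not shown that the two words are used for one quantity.

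**Conclusion.** The concern holds for incidence. The Abstract and Discussion claim more than the stated design can give: population or global incidence is unavailable at any sample size, because of how sites were chosen, which cases are excluded, and the absence of a population denominator. This conclusion needs no numerical assumption.

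Frequency per ED attendance or admission is not supported by the items listed, but could be obtained. The 20 000-per-site minimum leaves it anywhere from 7.4 down to 2.5 per 1000 for 5000 enrolled, if true attendances lie between one and three times the floor (an assumed range).

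The concern does not extend to the Box 1 aim as a whole. Prevalence among suspected cases is estimable, with a half-width of 1.2 points at an assumed 25% without clustering and 1.9 to 4.7 points for assumed ICCs of 0.01 to 0.10. What Box 1 lacks is a statement of which criterion counts as sepsis. The point is worth correcting because it changes what may be concluded, at little cost.

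**What to change.** 1. In the Abstract and Discussion, drop the word global and replace incidence with the frequency of suspected sepsis at participating EDs.
2. Add to the data collection an aggregate count, for each site, of paediatric ED attendances and of admissions through the ED over the study year, drawn from the attendance records already being screened. Report suspected sepsis per 1000 attendances and per 1000 ED admissions by site, with between-site variation. If these counts are already kept under the full protocol or the manual of operations, it is enough to say so.
3. In Box 1, state that prevalence means the proportion of enrolled suspected cases meeting each named criterion, with SIRS and Phoenix reported separately.

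The cost is a few aggregate numbers per site, which should be retrievable retrospectively, and a change of wording. Nothing changes in enrolment or in the data taken from each child's record. The price is a more modest claim: step 2 gives frequencies for these EDs and does not turn them into population incidence.

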### Patient recruitment, study procedures and data collection

ED attendance records will be screened at regular intervals, with a minimum frequency of every 14 days, by research staff to identify eligible patients (figure 1). The reference to missing data in the figure refers to the reason for exclusion. Participants meeting eligibility criteria will be enrolled in the study. Participant information will be stored in a secure, password-protected file at each local site, with personally identifiable information replaced with a unique study identification number.

